#### Testing procedures

In 2009, we carried out a cross-sectional comparison pilot study in two public hospitals in Cork, Ireland; one of which had implemented a long-term (2 years) catering intervention designed to reduce dietary fat, saturated fat, sugar and salt intake. All menus were modified. High-salt products (gravy mixes, stock cubes) and processed meat (bacon, corned beef) were replaced with low-salt options (turkey, chicken and fish). Fresh herbs, spices and garlic were introduced. Salt was removed in cooking. Saltcellars were removed from the tables in the canteen but small salt sachets were available at the service counter. Nutrition information was displayed in the canteen area. No sauces were added to any meals without the employee’s consent. All desserts were fruit-based. Staff members were encouraged to consume extra salad and vegetable options at no extra cost. Cooking methods with oil were reduced. No catering changes were implemented in the second hospital.

A total sample of 100 random employees aged 18 to 64 years (50 from each hospital) who consumed at least one main meal in the hospital staff canteen daily took part in the study. Dietary intakes and sociodemographic characteristics were assessed. Reported mean intakes of total sugars, total fat, saturated fat and salt were significantly lower in the intervention hospital when adjusting for age and sex. Estimated average salt intake in the intervention hospital (5.6 g/day) did not exceed the tolerable upper limit of 6 g/day vs. a mean salt intake of 6.7 g/day in the non-intervention hospital.

The study findings, published in the journal Public Health Nutrition [24], suggest that a structured catering initiative sustained over a relatively long period may influence long-term positive food choices at work and at home. Although these findings should be interpreted cautiously given the small sample size, many of the proposed dietary environmental modification and nutrition education components of the 'Food Choice at Work’ study have been shown to be acceptable and feasible in a workplace setting.

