#### Determination of sample size

A decrease in BMI by 1 kg/m^2^ (1 unit) and a 2 g average fall in dietary salt intake would have population health significance and clinical significance in terms of the risk of diet-related disease, for example, hypertension. To detect this difference in BMI between the control and intervention groups at follow-up session after 7 to 9 and 13 to 16 months and assuming a common standard deviation of 3.77, it is estimated that a sample size of 448 (112 per workplace) would have 80% power at the 5% significance level (findings from a previous study show that a 1 kg/m^2^ difference was independently associated with 13% higher risk for hypertension) [25,26]. The study will also be adequately powered (80% power at the 5% significance level) to detect a fall in dietary salt intake between the control and intervention groups at follow-up periods of 7 to 9 and 13 to 16 months using a standard deviation of 4.2 (In a previous intervention study the response within each participant group was normally distributed with standard deviation 4.2) [27].

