##### Unit of analysis

While the data will be collected at the individual level, the primary unit of analysis will be at the workplace level. Standard errors will be adjusted for clustering within the four workplaces before calculating confidence intervals.

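### The 80% power stated for salt makes no allowance for the clustering adjustment that the plan commits to; it is a safe floor only if clustering is ignored

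*Protocol article*

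**What the plan says.** The Determination of sample size section opens with the differences that matter: 1 kg/m² in BMI, and for salt "a 2 g average fall in dietary salt intake would have population health significance and clinical significance". It then sizes the trial on BMI, "assuming a common standard deviation of 3.77", and concludes that "a sample size of 448 (112 per workplace) would have 80% power at the 5% significance level".

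Salt follows as an additional statement: "The study will also be adequately powered (80% power at the 5% significance level) to detect a fall in dietary salt intake", "using a standard deviation of 4.2". That sentence does not repeat the 2 g and gives no group size of its own. The comparison is described only as control against intervention groups at the two later follow-ups, so it is unclear whether workplaces are compared singly or pooled. The section contains no ICC and no design effect.

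The Unit of analysis section makes the workplace the primary unit of analysis and adds: "Standard errors will be adjusted for clustering within the four workplaces before calculating confidence intervals". Under Modelling process and outcomes, each of the four conditions is given to exactly one workplace.

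**The concern.** The power statement and the analysis statement describe different calculations. One treats 448 employees as independent; the other promises standard errors that allow for employees of the same workplace resembling one another. This is not a detail left to an analysis plan, because the article states both the power figure and the adjustment, and the figure does not describe the adjusted analysis.

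What is at stake is how a null salt result would be read. A reader told that the study has 80% power for salt would take a non-significant result as reasonable evidence against a 2 g effect. Under the cluster-adjusted analysis that inference may not be available.

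**Working it through.** **Inputs from the Determination of sample size section.** Salt difference 2 g; salt SD 4.2 (no unit given, taken as g/day); 448 participants, 112 per workplace; 5% level, taken as two-sided because sidedness is not stated; target power 80%. **Assumed by this review:** the ICC values, since the document gives none.

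**Step 1: where 448 comes from.** Per-group n = 2 × (1.960 + 0.842)² × (SD/difference)². For BMI, 2 × 7.849 × 3.77² = 223.1, rounded up to 224, and 2 × 224 = 448. The total is thus reproduced by a two-group calculation with no clustering allowance.

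**Step 2: salt without clustering.**
- Required n: 2 × 7.849 × (4.2/2)² = 69.2, so 70 per group (71 by the t-distribution).
- Standard error for 112 against 112: 4.2 × √(2/112) = 0.561 g. The ratio 2/0.561 = 3.56 gives power 94.6% (normal) or 94.4% (t).
- Difference detectable at 80%: 2.802 × 0.561 = 1.57 g.
- Control against three pooled workplaces (112 v 336): 99.2%. Two against two (224 v 224): 99.9%.

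No grouping returns 80%; all exceed it.

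**Step 3: the ICC at which 80% is lost.** With 112 per workplace the design effect is 1 + (112 − 1) × ICC = 1 + 111 × ICC. The largest design effect compatible with 80% is (2/(2.802 × 4.2))² divided by (1/n₁ + 1/n₂).

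| Comparison | Largest design effect | Break-even ICC |
|---|---|---|
| 112 v 112 | 1.62 | (1.62 − 1)/111 = 0.0056 (0.0052 using n = 71) |
| 112 v 336 | 2.43 | (2.43 − 1)/111 = 0.013 |
| 224 v 224 | 3.24 | (3.24 − 1)/111 = 0.020 |

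**Step 4: salt power at assumed ICCs** (2 g, SD 4.2; each n divided by the design effect; t-distribution, with the normal approximation in brackets for 112 v 112).

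| Assumed ICC | Design effect | Effective n per workplace | 112 v 112 | 112 v 336 | 224 v 224 |
|---|---|---|---|---|---|
| 0 | 1.00 | 112 | 94% (95%) | 99% | 99.9% |
| 0.01 | 2.11 | 53 | 68% (69%) | 85% | 93% |
| 0.02 | 3.22 | 35 | 50% (51%) | 68% | 80% |
| 0.05 | 6.55 | 17 | 27% (29%) | 39% | 49% |

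**Step 5: why even these are optimistic.** The design-effect formula treats the between-workplace variance as known and keeps degrees of freedom at the level of individuals. With one workplace per condition, that variance cannot be separated from the intervention effect, so the trial cannot supply it.

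**The case against.** The strongest defence is that the salt sentence is a secondary adequacy check on a sample sized for BMI, so 80% means at least 80%. That stands as far as it goes. Without clustering about 70 per group suffice and 112 are planned.

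Several stronger readings are therefore tempting but unsupported:

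- **That the 80% is an arithmetic error because one sample size cannot give 80% for both outcomes.** A sample driven by the smaller standardised difference (1/3.77 = 0.27 for BMI) will naturally exceed 80% for the larger one (2/4.2 = 0.48 for salt). Missing exactly 80% is loose wording.
- **That 80% holds only at one particular ICC.** It holds at every ICC up to the break-even value.
- **That the break-even is 0.005 whatever the comparison.** The section does not fix the grouping. At an assumed ICC of 0.01, both pooled comparisons still exceed 80%.
- **That power is owed at the pilot's contrast.** The Testing procedures section reports 5.6 g/day in the intervention hospital "vs. a mean salt intake of 6.7 g/day in the non-intervention hospital", a gap of 1.1 g. That came from a cross-sectional comparison of 50 employees per hospital, which the authors themselves treat with caution. The plan names 2 g as the difference that matters and need not be powered for a smaller one.

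It can also be objected that any ICC inserted is a guess. That is fair, and is why the figures must be labelled as assumed. It does not rescue the 80%, because the floor argument works only when the promised clustering adjustment is left out.

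**Conclusion.** The point holds in a limited form. The salt power statement is true with margin for an unclustered comparison (about 94% for 112 against 112, 2 g, SD 4.2, two-sided 5%), but it does not describe the cluster-adjusted analysis that the same article commits to. For one workplace against one, 80% is lost above an ICC of about 0.005; at assumed ICCs of 0.01 to 0.05 power is about 68% to 27%. Pooled comparisons tolerate more, up to about 0.013 or 0.020.

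The unclustered figures rest only on the article's inputs, a two-sided test and reading the 2 g into the salt sentence. The clustered figures rest also on assumed ICCs and on a formula that flatters a design with one workplace per condition. The documents do not show that salt is underpowered, because they give no ICC; they show that adequate power has not been established for the planned analysis. This should be corrected, as a matter of accurate statement rather than of sample size.

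**What to change.** In the Determination of sample size section:

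1. Name the 2 g difference in the salt sentence, and state which comparison is meant (one workplace against control, or a stated pooling).
2. Replace the 80% with: 94% power for 112 against 112 before any allowance for clustering.
3. Add power over a range of ICCs explicitly labelled as assumed, for instance about 68%, 50% and 27% at 0.01, 0.02 and 0.05 for 112 against 112, or the matching figures if a pooled comparison is chosen.
4. State that with one workplace per condition the between-workplace variance cannot be separated from the intervention effect, so the clustered figures are optimistic and a null salt result should not be read as adequately powered.

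This costs wording only and needs no further participants. The downside is that the restated figure is less favourable than the present one.

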### Evaluation

The third phase is concerned with assessing the (1) effectiveness of the interventions, (2) understanding the change process and (3) assessing the cost-effectiveness of the complex intervention.

#### Effectiveness of the interventions

##### Study design

Effectiveness of the interventions will be evaluated using a clustered controlled trial design in four large manufacturing multinational workplaces based in Cork in the Republic of Ireland with a representative sample of employees.

##### Study duration

The total study duration is 16 months, with the interventions being delivered over a 9-month period. Follow-up is for 6 months post-intervention.

##### Unit of analysis

While the data will be collected at the individual level, the primary unit of analysis will be at the workplace level. Standard errors will be adjusted for clustering within the four workplaces before calculating confidence intervals.

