#### Modelling process and outcomes

This behavioural complex intervention design is guided by the detailed principles and recommendations of the NICE guidelines [1]. The study focuses on two potential methods to improve long-term dietary behaviour in the workplace including environmental dietary modification and nutrition education. Both methods will be measured independently and collectively in purposively selected workplaces. Workplace A (the control) will continue to follow usual practice. No changes will be implemented. Workplace B will receive nutrition education. Workplace C will receive nutrition education and environmental dietary modification. Workplace D will receive environmental dietary modification alone. The intervention design has been developed by the research team (nutritionists, dieticians, public health and health promotion researchers), catering stakeholders in Ireland (representatives of the Catering Managers Association of Ireland), workplace stakeholders (catering managers, human resources managers, occupational health managers) and the target population, that is manufacturing employees. Figure 2 illustrates the trial design.

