### Implications for research and practice

The Food Choice at Work interventions may improve the included employees’ dietary behaviours and reduce their diet-related disease risks. This study will provide critical evidence of the effectiveness of workplace complex interventions in the promotion of healthy dietary behaviours in the manufacturing working population. It may assist in the development of future guidelines to improve dietary behaviours in the workplace and will inform future researchers. It may influence national and international catering stakeholders, policy makers and motivate the food industry to provide healthier food choices. If the findings are positive, it may reduce diet-related disease development and the burden on the healthcare system in the Republic of Ireland. The large multinational manufacturing companies included in the study have similar worldwide structures and operations; the findings, therefore, will be generalizable nationally and transferable internationally. Following study completion, it is planned to examine the transferability of this complex intervention in a European or global context.

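### With one workplace per condition, the planned workplace-level analysis and clustering adjustment cannot be estimated for the contrasts in the study hypothesis

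*Protocol article*

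**What the plan says.** The Study design section describes a "clustered controlled trial design in four large manufacturing multinational workplaces". Under Modelling process and outcomes, each condition is one site: "Workplace A (the control) will continue to follow usual practice", "Workplace B will receive nutrition education", "Workplace C will receive nutrition education and environmental dietary modification", and D receives the environmental component alone. The Recruitment section says that workplaces are selected and allocated purposively.

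The Unit of analysis section says that data are collected on individuals but "the primary unit of analysis will be at the workplace level", and then that "Standard errors will be adjusted for clustering within the four workplaces before calculating confidence intervals". It does not name the method of adjustment.

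The Study hypothesis section is about the combined intervention against each component alone, that is, C versus B and C versus D. The Statistical analysis section plans repeated-measures ANOVA and a mixed effects model for variation between subjects over time, adjusted for factors such as age, sex and shift pattern. It mentions no random effect for workplace.

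The Limitations section admits non-randomisation, lack of concealment and lack of blinding, and relies on the sites being similar. It does not say that workplaces are unreplicated within a condition. Implications for research and practice says that "the findings, therefore, will be generalizable nationally and transferable internationally".

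**The concern.** A clustering adjustment needs information on how much workplaces differ when they receive the same condition. That information comes only from having at least two workplaces in some condition, or from assuming a structure that pools conditions. Here there is one workplace per condition and no such assumption is stated.

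The section governs the primary confidence intervals. Followed literally, it yields either no interval or, under one common software option, an interval that is far too narrow. A reader told that intervals are adjusted for clustering would take them to cover differences between workplaces unrelated to the intervention, such as a change of caterer, a change in shift pattern or a local health drive. They cannot cover this.

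**Working it through.** **Inputs from the protocol.** 4 workplaces, 4 conditions, 112 participants per workplace, BMI standard deviation (SD) 3.77, difference 1 kg/m², 5% level (taken as two-sided), 80% power. No ICC or design effect is given; the ICCs below are assumptions.

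**The plan's own figure.** The sample size section says that "a sample size of 448 (112 per workplace) would have 80% power". For two independent means, n per group = 2 × (1.960 + 0.842)² × 3.77² / 1² = 223.1, so 224, and 2 × 224 = 448. The total therefore reproduces as two groups of independent individuals. (The one-sample formula gives 111.6, so 112, and 4 × 112 is also 448.) Neither route includes a design effect.

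**Reading 1: workplace-level summaries.** Four workplace values and four condition means leave 4 − 4 = 0 residual degrees of freedom. A pairwise contrast leaves 2 − 2 = 0. No standard error (SE) exists for any arm contrast.

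**Reading 2: random workplace effect plus arm.** With between-workplace variance τ², SE(B − A) = √[2 × (τ² + 3.77²/112)].

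| τ² | SE(B − A) |
|---|---|
| 0 | 0.50 |
| 0.1 | 0.67 |
| 0.5 | 1.12 |
| 1 | 1.50 |
| 5 | 3.20 |

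On simulated data, the restricted log-likelihood was identical to six decimals at all five values of τ². The data cannot choose among them, so the SE is arbitrary.

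**Reading 3: sandwich SE clustered by workplace, with arm terms.** Least-squares residuals sum to zero within each workplace, so each cluster's contribution to the sandwich is zero. Simulation used 4 × 112, SD 3.77, no intervention effect, t on 3 df, and ICC 0, 0.01 and 0.05:

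- Arm terms only: SE about 6 × 10⁻¹⁴ against an ordinary SE of about 0.50; false rejection 100%. A before-after arm-by-time model behaved the same way.
- Age and sex added, similar across sites: SE about 0.02 to 0.03; false rejection about 85% to 95%.
- Age and sex differing across sites (assumed between-site SD of 5 years and 15 percentage points): SE about 0.10; false rejection about 50% to 65% at ICC 0 and 0.01.

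The covariate results depend on a covariate distribution that the protocol does not give.

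**Reading 4: ordinary individual-level SEs.** For 112 versus 112, the ratio of true to ordinary SE is f = √[(1 + 111 × ICC)/(1 − ICC)], and the type I error is 2 × [1 − Φ(1.96/f)].

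| Assumed ICC | f | Type I error |
|---|---|---|
| 0 | 1.00 | 5% |
| 0.005 | 1.25 | 12% |
| 0.01 | 1.46 | 18% |
| 0.02 | 1.81 | 28% |
| 0.05 | 2.63 | 46% |

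These are for a single cross-sectional comparison. In an analysis of change, stable workplace differences cancel and only workplace-by-time variation remains. The same formula applies, but with the ICC of change.

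**Can pooling rescue it?** A 2 × 2 model with main effects only leaves 4 − 3 = 1 df (critical t 12.7). Control versus the other three pooled leaves 4 − 2 = 2 df (critical t 4.3). The protocol specifies neither. The second does not compare C with B or D, and the first can do so only by assuming that the two components do not interact.

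**The case against.** The strongest reply is that the Unit of analysis section is one condensed sentence, names no estimator, and may be filled in by an analysis plan not shown. That stands against one tempting reading. A reader might infer that the trial is committed to a sandwich SE by workplace and will therefore report false significance. The document does not say so, and an SE of 10⁻¹⁴ would be obvious in the output. The result for Reading 3 is conditional. But no choice of estimator supplies replication that the design lacks, so the adjustment fails under the other usual readings too.

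A second reply is that the outcomes are changes, so the 18% and 46% figures may overstate the problem. This also stands: they illustrate assumed cross-sectional ICCs and are not the trial's error rates. They do not go away altogether, because workplace-specific changes over the study period remain fully confounded with condition.

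Third, the Statistical analysis section already plans something close to a workable analysis, with repeated measures on individuals and covariate adjustment. That is correct and makes the repair small, but the section on unit of analysis contradicts it.

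Fourth, a reader might add low power to this point. For 112 versus 112, power for 1 kg/m² is about 51% at ICC 0, because 448 reproduces as 224 versus 224. That shortfall arises without any clustering and is a separate issue.

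Finally, the generalisability sentence argues from similar company structures, not from the intervals. It needs qualifying and need not be deleted.

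**Conclusion.** The point holds in this form: the stated workplace-level analysis and clustering adjustment cannot be estimated for C versus B, C versus D or any other pairwise contrast. This follows from one workplace per condition and needs no assumed number. More employees per site would not cure it.

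The size of the consequence depends on what is done instead. A sandwich SE, if chosen, gives false rejection of 100% with arm terms only and roughly 50% to 95% with age and sex in the runs above. Ordinary individual-level SEs give about 12% to 46% for assumed cross-sectional ICCs of 0.005 to 0.05; the figure for change is unknown and may be lower. The documents do not support saying that the trial will produce falsely significant results, only that the promised adjustment cannot be delivered. The Limitations section does not disclose this.

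**What to change.** 1. Replace the Unit of analysis section so that it agrees with the Statistical analysis section: analyse individuals, with repeated measures within participant, and estimate differences in change between the four named workplaces. Apply no workplace-level cluster-robust SE and no workplace random effect.
2. State there that the intervals exclude between-workplace variation and that condition is fully confounded with workplace. Add the lack of replication to Limitations.
3. Add a sensitivity table that multiplies the ordinary SE by √[(1 + 111 × ICC)/(1 − ICC)] for an assumed ICC of change from 0.005 to 0.05 (factors about 1.25 to 2.63), labelled as an assumption.
4. Qualify the sentence on generalisability so that it does not rest on these intervals.

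The cost is wording and one table, with no new sites or data. The downside is a more modest conclusion: differences between four particular workplaces, with the attribution to the intervention argued and not covered by the interval.

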##### Recruitment

A comprehensive list of manufacturing companies in Cork in the Republic of Ireland will be obtained from the Industrial Development Authority of Ireland (IDA) website. Workplaces will be systematically selected from the A to Z listing. As the focus of the study is to implement a complex dietary intervention in an ideal environment, workplaces will be purposively selected and allocated. Only workplaces and employees that meet the specified selection criteria will be recruited.

